### Operational considerations

In case of new intracranial tumour activity, patients in both treatment arms may receive additional WBRT or GKRS at the discretion of the treating radiation-oncologist.

## Discussion

Over the past decade, the management of patients with brain metastases has changed substantially. WBRT has long been the mainstay of treatment, especially in patients with more than 3 or 4 brain metastases. However, increasingly more patients with brain metastases are treated with SRS. SRS is well established in patients with a limited number of brain metastases (1–4) and research on SRS in patients with multiple (> 4) brain metastases is growing steadily. According to the *American Society for Radiation Oncology* (ASTRO) and the *National Comprehensive Cancer Network Clinical Practice Guidelines in Oncology* (NCCN) there now is growing evidence suggesting that the cumulative *volume* of the brain metastases, rather than the *number* of brain metastases, is a better selection criterion for SRS. Accordingly, the NCCN guideline no longer specifies an upper limit for the number of brain metastases [38, 39].

In addition, concerns about the potential late adverse effects of WBRT on cognitive function has led to decreased use of (adjuvant) WBRT. Compared to WBRT, SRS has a better ability to spare healthy tissue because of the high level of precision and quick dose fall-off. Therefore, few(er) negative cognitive side-effects could be expected after treatment with SRS.

Cognitive functions are essential to our daily functioning and quality of life. Since more patients with brain metastases live longer after treatment, reducing or preventing (late) cognitive side effects is of great importance. CAR-Study B will yield information on which treatment modality, GKRS or WBRT, best preserves cognitive functions and quality of life of these patients. In addition to survival and tumour related outcomes, CAR-Study B measures relevant clinical outcomes, such as depression, anxiety and fatigue which are important psychological factors that may influence cognitive functioning [54]. Together with other trials, CAR-Study B may help diminish the controversy about the role of SRS versus WBRT in the management of multiple BM.

We chose the 3-months primary endpoint because *early* effects of radiation on cognition, albeit mostly transient, can negatively affect patients’ quality of life. Moreover, at this point in time we will be able to assess cognitive function in as many of the patients enrolled, maintaining the highest possible statistical power.

The more persistent *late delayed* effects of radiation on cognitive functioning become apparent 6–12 months after treatment [22] and may be most disruptive for patients’ quality of life. For this reason, we have also included long-term assessments in our design. Information on test performance in long-term survivors is essential for complete comprehension of the course of cognitive functions over time, even though many of the enrolled patients may have deceased at this point in the study.

This study may be highly relevant in clinical decision-making; knowledge gained from this trial may possibly change clinical practice and international guidelines on BM. For example, thus far in the Netherlands, the standard of care for patients with multiple brain metastases (> 4) has remained WBRT. Ultimately, the purpose of CAR-Study B is to inform patients and doctors which treatment modality, GKRS or WBRT, best preserves cognitive functions and quality of life. This will enable patients and doctors to make shared treatment decisions grounded on scientific evidence and consequently maximize the clinical outcome of each individual patient.

## Appendix

For the Bayesian stopping rule, a weakly informative prior is employed with Beta(2.09,2.91)-distributions for both treatment groups. This prior contains the same amount of information as the prior of Chang et al. (2009). Furthermore, the prior mean is equal to 0.42 which is the sample average of the failure rates based on the results of Chang et al. The prior is displayed in Fig. 2.

The trial is terminated prematurely when the probability of the event that the failure rate of one treatment group, as computed under the Bayesian model, is higher than the failure rate of the other treatment group is greater than 0.975. Following Chang et al. an effect size of 0.30 is expected. A power analysis of the Bayesian stopping rule revealed the expected Bayesian probability as a function of the sample size n (Fig. 3). The figure shows that for *n* = 46 (23 patients in each group) and using a 0.3 effect size, it is expected that there is a 0.975 probability that the failure rate of WBRT treatment as found in the study is larger than the failure rate of GKSR treatment. Hence, we deem early stopping relatively likely if the effect sizes are comparable to earlier accounts in the literature.

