### Statistical methods

The Bayesian power analysis and interim analyses are based on the randomised trial by Chang and colleagues [45]. An independent statistician will do interim monitoring of this trial using Bayesian statistical methods [51, 52]. Each patient’s HVLT-R total recall score recorded at 3 months is assigned a binary outcome: A decline in the total recall score of 5 points or greater compared with baseline will be considered a *failure* (0). A stable or improved score, or a decline of 4 points or less compared with baseline will be considered a *success* (1). The failure rate for treatment *k* is designated *qk*. The prior failure rates for both treatment groups will be modelled as Beta(2.09, 2.91)-distributions, with a mean of 0.42 for both groups (for details see Appendix). During the trial, stopping rules specify that in the case of a probability greater than 0.975 for the event that the failure rate of one treatment group is higher than the failure rate of the other treatment group, we will stop randomising patients to that treatment-arm. In this case, the study is terminated prematurely and the central research question will be answered. If the effect sizes are comparable to earlier accounts in the literature (following Chang et al. an effect size of 0.30 is expected), the early stopping rule will likely come into effect when 46 patients are enrolled (23 patients at 3-months follow-up in both groups; for details see Appendix).

Group analyses are carried out on an intent-to-treat principle. Raw cognitive test scores are compared with published normative values according to age (and, if available, to education) and converted into standardized scores. Cognitive impairment is defined as test performance at or below − 1.5 SD from the normative mean [6, 53]. Reliable change indices (RCI), reflecting change at the individual level in the context of observed changes based on published normative data, correcting for measurement errors are calculated, since group results may mask the variability in individual responses to the intervention [44]. Number of patients, who have improved versus the number of patients who remained stable, or declined, will be counted for all follow-up assessments. These will be compared over conditions with chi-square tests.

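### The 0.975 behind the 46 patients is a posterior probability at the expected data, not power; the chance of meeting the stopping rule is roughly even

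*Protocol article*

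**What the plan says.** The Statistical methods section of the protocol article sets a stopping rule that is monitored during the trial by an independent statistician. Randomisation to an arm stops "in the case of a probability greater than 0.975 for the event that the failure rate of one treatment group is higher" than that of the other arm. A failure is a fall of at least 5 points in HVLT-R total recall at 3 months. On the prior, the Appendix says that "a weakly informative prior is employed with Beta(2.09,2.91)-distributions for both treatment groups", and that "the prior mean is equal to 0.42 which is the sample average of the failure rates" in the earlier trial. It adds that "an effect size of 0.30 is expected".

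The Appendix then describes a power analysis whose output is the expected Bayesian probability plotted against sample size (Fig. 3, not shown in the text at hand). At 46 patients, "it is expected that there is a 0.975 probability that the failure rate of WBRT treatment as found in the study is larger" than that of the radiosurgery arm. It continues: "Hence, we deem early stopping relatively likely if the effect sizes are comparable to earlier accounts in the literature". The Statistical methods section repeats the conclusion: "the early stopping rule will likely come into effect when 46 patients are enrolled (23 patients at 3-months follow-up in both groups".

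The article gives no other justification for 46 patients, and it nowhere states a probability of meeting the criterion.

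**The concern.** Power is the probability, over repeated trials, that the criterion is met. The Appendix reports something else: how large the posterior probability would be if the data came out as expected. That value sits on the threshold itself, so chance variation puts about half of trials with a true 0.30 difference below it. The step from 0.975 to *likely* therefore treats one kind of probability as the other.

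At stake is the only stated rationale for the sample size. A reader, funder or ethics committee would take the trial to be well placed to meet its own criterion if the assumed effect is real. In fact a trial with a true 0.30 difference has something like a 40% to 53% chance of not meeting it, depending on how often the data are looked at.

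**Working it through.** **Inputs.** Prior Beta(2.09, 2.91) in each arm, worth 5 pseudo-observations, with mean 2.09/5 = 0.418. Threshold 0.975. Difference 0.30. 23 patients per arm at 3 months. All are in the Statistical methods section or the Appendix. *Assumption:* the article does not give the two arm rates. I centre them on the stated average of 0.42, so WBRT is 0.42 + 0.15 = 0.57 and GKRS is 0.42 − 0.15 = 0.27. Other 0.30-difference pairs serve as sensitivity checks.

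**Model.** With x failures among 23 patients, the posterior in an arm is Beta(2.09 + x, 2.91 + 23 − x). The monitored quantity is P(q_WBRT > q_GKRS) = ∫ f_WBRT(q) F_GKRS(q) dq, evaluated numerically.

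**Step 1: reproduce the stated 0.975.**
- Expected counts: 23 × 0.57 = 13.11 and 23 × 0.27 = 6.21.
- Posteriors: Beta(15.20, 12.80) and Beta(8.30, 19.70).
- P(q_WBRT > q_GKRS) = 0.972.
- Hand check by normal approximation: the posterior means differ by (15.20 − 8.30)/28 = 0.246. The variance is (0.543 × 0.457 + 0.296 × 0.704)/29 = 0.0157, so the SD is 0.125. Then z = 1.96, which corresponds to about 0.975.
- At whole counts of 13 and 6 the exact value is 0.974.
- Over pairs from 0.65/0.35 to 0.50/0.20 it runs from 0.970 to 0.976.

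The published figure is therefore the posterior at the expected data.

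**Step 2: average over the data instead.** Weighting the posterior probability of each of the 24 × 24 possible outcomes by its binomial probability under 0.57 and 0.27 gives 0.924. A literal expected value is thus about 0.92, not 0.975.

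**Step 3: chance of meeting the rule at one look.** This is the sum of the binomial weights of all outcomes with a posterior above 0.975.

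| True rates (WBRT / GKRS) | Difference | P(posterior > 0.975), 23 per arm |
|---|---|---|
| 0.65 / 0.35 | 0.30 | 44% |
| 0.57 / 0.27 | 0.30 | 47.5% |
| 0.50 / 0.20 | 0.30 | 53% |
| 0.545 / 0.295 | 0.25 | 34% |
| 0.52 / 0.32 | 0.20 | 22% |
| 0.495 / 0.345 | 0.15 | 13% |

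**Step 4: allow for interim looks.** The article gives no look schedule. Cumulative chance of crossing by 23 per arm, for 0.57 and 0.27, from 200,000 simulated trials:

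| Looks (patients per arm) | Chance of crossing |
|---|---|
| 23 only | 47% |
| 12, 23 | 50% |
| 15, 23 | 52% |
| 10, 15, 20, 23 | 55% |
| every pair from 5 to 23 | 60% |

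**Step 5: scale.** For the same rates at a single look, an 80% chance would need about 44 per arm (88 in total). With 20 evaluable patients per arm instead of 23, the chance is 44%.

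**The case against.** The strongest reply is that the rule is applied during the trial, so the relevant figure is the cumulative chance of stopping by 46 patients, not the chance at one look. That stands. At 55% to 60% under frequent looks, *relatively likely* is weak wording rather than plainly false. A reader might infer from the single-look 47% that the trial is more likely than not to miss its criterion. The documents do not support that reading: monitoring is planned, and one interim look already brings the odds to even.

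The arm rates are also an assumption. Lower pairs with the same difference do better at one look: 56% at 0.45/0.15 and 59% at 0.40/0.10. These average 0.30 and 0.25, well below the stated 0.42. With repeated looks, 0.50/0.20 reaches 59% (four looks) to 63% (every pair). None of this comes near a conventional 80%.

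A reader might also infer that the 0.975 was miscalculated, or that the article claims 97.5% power. Neither holds. The number reproduces, and the Appendix names it as an expected Bayesian probability. The fault lies in calling the exercise a power analysis and in the inference drawn from it. Nor does much rest on the phrase about the rate found in the study, because the Appendix also says that the probability is computed under the Bayesian model. Finally, nothing in the article says that failure to cross would be read as no difference, so that misreading remains only a risk.

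**Conclusion.** The point holds in this form. The 0.975 is the posterior probability at the expected counts and coincides with the threshold, so it cannot support the claim that the rule will likely be met. If the true difference is 0.30 and 23 patients per arm are evaluable, the chance of meeting the rule is roughly even: about 47% at a single look (44% to 53% for pairs from 0.65/0.35 to 0.50/0.20). For rates of 0.57 and 0.27 it is about 50% to 60% cumulatively, depending on the looks. It falls quickly if the difference is smaller. These figures rest on arm rates centred on 0.42 and on look schedules chosen for illustration, since the article states neither. That the odds are near even does not depend on the exact pair, because it follows from placing the expected result on the threshold.

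**What to change.** - State the assumed failure rate in each arm.
- In the Appendix, replace the 0.975 statement with the probability that the criterion is met at 23 evaluable patients per arm, both at a single look and cumulatively under the planned looks. For example: *with failure rates of 0.57 and 0.27, the probability that the 0.975 criterion is met is about 47% at a single look and up to about 60% if checked after every pair*. The second figure should be recomputed for the actual schedule.
- Redraw Fig. 3 as the probability of meeting the criterion against sample size, for differences from 0.15 to 0.30.
- In the Statistical methods section and the Appendix, replace the statements that stopping is likely with *roughly even odds* or the computed figure.

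The cost is some rewording and one recomputed figure. The stated design property becomes less favourable, but no extra patients are needed and the stopping rule itself does not change.

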## Abbreviations

BM: Brain metastases
CTCAE: Common Terminology Criteria for Adverse Events
GKRS: Gamma Knife Radiosurgery
Gy: Gray (unit of radiation)
KPS: Karnofsky Performance Status
MRI: Magnetic Resonance Imaging
NTR: Netherlands Trial Registry
SRS: Stereotactic Radiosurgery
WBRT: Whole Brain Radiation Therapy
